## Abstract

**Background:**

Mental health disorders are common and disabling for young people because of the potential to disrupt key developmental tasks. Implementation of evidence-based psychosocial therapies in New Zealand is limited, owing to the inaccessibility, length, and cost of training in these therapies. Furthermore, most therapies address one problem area at a time, although comorbidity and changing clinical needs commonly occur in practice. A more flexible approach is needed. The Modular Approach to Therapy for Children with Anxiety, Depression, Trauma, or Conduct Problems (MATCH-ADTC) is designed to overcome these challenges; it provides a range of treatment modules addressing different problems, within a single training program. A clinical trial of MATCH-ADTC in the USA showed that MATCH-ADTC outperformed usual care and standard evidence-based treatment on several clinical measures. We aim to replicate these findings and evaluate the impact of providing training and supervision in MATCH-ADTC to: (1) improve clinical outcomes for youth attending mental health services; (2) increase the amount of evidence-based therapy content; (3) increase the efficiency of service delivery.

**Methods:**

This is an assessor-blinded multi-site effectiveness randomized controlled trial. Randomization occurs at two levels: (1) clinicians (≥60) are randomized to intervention or usual care; (2) youth participants (7–14 years old) accepted for treatment in child and adolescent mental health services (with a primary disorder that includes anxiety, depression, trauma-related symptoms, or disruptive behavior) are randomly allocated to receive MATCH-ADTC or usual care. Youth participants are recruited from ‘mainstream’, Māori-specific, and Pacific-specific child and adolescent mental health services. We originally planned to recruit 400 youth participants, but this has been revised to 200 participants. Centralized computer randomization ensures allocation concealment. The primary outcome measures are: (i) the difference in trajectory of change of clinical severity between groups (using the parent-rated Brief Problem Monitor); (ii) clinicians’ use of evidence-based treatment procedures during therapy sessions; (iii) total time spent by clinicians delivering therapy.

**Discussion:**

If MATCH-ADTC demonstrates effectiveness it could offer a practical efficient method to increase access to evidence-based therapies, and improve outcomes for youth attending secondary care services.

**Trial registration:**

Australian and New Zealand Clinical Trials Registry ACTRN12614000297628.

## Background

Mental health problems are common in children and adolescents (youth) and the impact is considerable [1–5], with an estimated 50 % of all adult mental health disorders having an onset in adolescence [6]. A number of evidence-based therapies exist for the most common youth mental health problems, namely anxiety, depression, trauma-related symptoms, and disruptive behavior [1]. The Ministry of Health in New Zealand has repeatedly asserted the need for evidence-based treatments in mental health [7–9], including in child and adolescent mental health services [9]. There is evidence for the effectiveness of cognitive behavioral therapy for anxiety, depression, and trauma-related symptoms, while behavioral parent training is the treatment of choice for disruptive behavior [10–13]. Although these therapies have been shown to be effective in research settings, they are challenging to implement in clinical practice [14, 15]. For instance, most traditional evidence-based therapies focus on one disorder (or a small cluster of related disorders), making it difficult for clinicians to address heterogeneous caseloads, client comorbidities, and changes in clinical presentation during therapy [16]; training for each single-focus therapy can be time consuming and costly; and research participants in randomized controlled trials are typically treated for one disorder (whereas in clinical practice comorbidity is common).

New Zealand’s Child and Adolescent Mental Health Services (CAMHS) provide secondary level services for the 3–5 % of those with the most severe mental health problems aged 0–19 years [17]. The two largest professional groups employed in these services are nurses and social workers [18]; however, their pre-registration courses do not include training in psychotherapies specifically for youth [19]. Therefore, most learning occurs ‘on the job’. Furthermore, for clinicians to effectively treat a diverse caseload, they would need to train in multiple therapies, which is expensive and takes several years. For example, training in cognitive behavioral therapy is available in New Zealand in a one-year postgraduate course, which can be accessed by up to 12 clinicians per year. Accredited training in ‘Incredible Years’ (a form of evidence-based parent management training [20]) takes a year to complete and can be accessed by about 35 clinicians per year. Little training is available outside these courses and what exists will reach only a small minority of the approximately 1,000 full-time equivalent CAMHS clinicians in New Zealand [18]. The extent to which evidence-based therapies are currently used in CAMHS is not known, but based on clinicians’ access to training, and from overseas research [21–23], it is likely to vary across services and be limited by staff members’ past training, and may not be acceptable or effective for Māori (the indigenous people of New Zealand) or Pacific (people from the Pacific region) populations. Moreover, to meet the projected doubling of the demand on mental health services by 2020, treatment needs to be delivered more effectively and efficiently [24].

The Modular Approach to Therapy for Children with Anxiety, Depression, Trauma, or Conduct Problems (MATCH-ADTC) is a treatment system designed to work in day-to-day practice across a range of clinical problems [25]. MATCH-ADTC was developed following a number of meta-analyses of therapies with the best evidence of effectiveness [15, 26, 27] and following efforts to identify frequently used common elements of evidence-based practices for children and adolescents [28]. MATCH-ADTC was specifically designed to combine common elements of treatments for anxiety, depression, trauma-related symptoms, and disruptive behavior in one protocol, cater for comorbidity, and provide an opportunity to address fluctuations in presenting symptoms that might emerge during therapy [25, 29]. MATCH-ADTC comprises modules (i.e., specific practice elements) that can be organized in a flexible manner. Clinicians are guided by a MATCH-ADTC expert and an evidence-based algorithm to tailor treatment to each youth’s characteristics and needs. Youths and their families are also given an integral role in defining the goals of therapy. Furthermore, clinicians use a web-based system to monitor youths’ progress and adapt therapy until a problem is resolved. MATCH-ADTC has been evaluated in a randomized controlled trial (*n* = 174) comparing it against standard (single-focus) evidence-based therapies and usual care in the USA. The results showed that MATCH-ADTC was significantly more effective than standard evidence-based therapies and usual care, with effect sizes of 0.59–0.71 on primary outcome variables [30]. Furthermore, superiority relative to usual care was maintained in two-year follow-up analyses [31].

Our objective is to improve the overall quality of care received by youth attending CAMHS in New Zealand, by demonstrating improved clinical outcomes, increased efficiency of services, and increased delivery of evidence-based therapy. We have used Donabedian’s framework of structure, process, and outcome [32] to determine the potential impact of delivering MATCH-ADTC in New Zealand. In this study, our focus is on outcomes and process. We designed this trial to assess the effectiveness of MATCH-ADTC in the New Zealand context and we aimed in particular to investigate the acceptability and effectiveness for Māori and Pacific people. New Zealand has a growing Māori and Pacific population [33, 34], who are at increased risk of mental health problems [35–40], yet seldom specifically included in randomized controlled trials. In New Zealand, mental health services are delivered through ‘mainstream’ services. In some areas with large Māori and Pacific communities, there are specialized Kaupapa Māori and Pacific clinics (services that use delivery frameworks that are based on Māori or Pacific philosophies, values, and cultural practices).

This trial will contribute to the international literature by: (a) testing the effectiveness of MATCH-ADTC in publicly funded mental health services (a healthcare delivery model that is different from that used in the USA); and (b) providing information about the effectiveness of MATCH-ADTC across different ethnic groups.

### Primary hypotheses

We hypothesize that training CAMHS clinicians in MATCH-ADTC compared with usual care will:i.Improve clinical outcomes for children and adolescents accessing CAMHS (outcomes); we will determine this by comparing the trajectories of change in clinical severity for the MATCH-ADTC and usual care groups (i.e., determining which group improves more quickly).ii.Increase the delivery of evidence-based therapy (proces*s*); this will be measured by assessing the evidence-based content of recorded therapy sessions.iii.Yield equal or better efficiency of service delivery (process); this will be measured by clinician time (in minutes) to deliver therapy, and duration (in weeks) of contact with the service by children or adolescents, and their families.

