### Outcomes and measures

#### Primary outcomes

The three primary outcomes each address one of the three central aims of the trial: (i) the difference in trajectory of change of clinical severity between groups, using the parent-rated Brief Problem Monitor [42]; (ii) clinicians’ use of evidence-based content during therapy sessions (based on audio-recorded therapy sessions); (iii) total time spent by clinicians delivering therapy (using therapy logs).

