### Sample size

Overall, a sample size of 60 clinicians and 400 patients will provide sufficient power to detect effect sizes of approximately 0.37, well below the effect size shown by the comparable USA study [30]. The initial power calculation was to allow independent analysis to be undertaken for Māori and Pacific participants and ensured sufficient power (80 %) to detect moderate effect sizes of between 0.61 and 0.70 as statistically significant (two-tailed *α* = 0.05) in these groups (equivalent to the effect sizes found in the USA study [30]). This estimate allowed for a 15 % attrition rate in clinicians and in clients (based on the 12.3 % attrition rate reported in Weisz *et al.* [30] and adjustment for the clustering of patients with clinicians (intraclass coefficient = 0.1)). We assumed approximately six to eight patients per clinician (approximately 400 patients). If fewer clinicians were available within the targeted services, we planned to increase the number of participants per clinician to ensure that we maintained statistical power. The intention was to recruit approximately 12 clinicians working in Kaupapa Māori services and approximately 12 clinicians working in Pacific services. While this seemed feasible in the planning stages, when we were actually conducting the trial, there were a number of staffing difficulties in the services overall, and these impacted more particularly in the Kaupapa Māori and Pacific services, perhaps because of the smaller pool of people in the workforce. This led to difficulty in recruiting clinicians working in Māori and Pacific services, with resulting reduced ability to recruit participants to the trial from those services. It became evident that we would not reach the targets for Māori and Pacific participants to allow ethnic-specific analysis, as planned. An interim blinded-to-treatment allocation, single group, power analysis was undertaken (when approximately 50 participants had completed treatment) to determine the total number of participants needed to show overall clinical effectiveness for the whole sample. This summary produced a standard deviation for the change in the parent-rated Brief Problem Monitor of 4.4, which indicated that to show a clinically important difference in the change (>2 units) as statistically significant (two-tailed *α* = 0.05) with 80 % power, a total sample size of 160 participants would need to be recruited. A total sample of 200 participants would provide 90 % power for this comparison. Although a reduced final sample size would compromise the ethnic-specific analysis, it was felt that the primary question of whether MATCH-ADTC improved the trajectory of change of clinical severity more than usual care could be conclusively addressed with 200 participants. Based on the ongoing recruitment, it was anticipated that this total recruitment could be achieved if we extended the timeline and recruited until the end of June 2015.

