##### Efficiency of service delivery

Efficiency in delivery of therapy for MATCH-ADTC and usual care will be compared using ANOVA to test for significant differences using the following data which will be collected from the clinical service, including:Clinician time (in minutes);Duration of contact with the service (in weeks);Number of therapy sessions; andNumber of missed therapy sessions.

If any of these outcomes do not meet the assumptions for parametric ANOVA models, the data will be transformed as appropriate prior to analysis.

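### The efficiency hypothesis is worded as equal or better in one place and as an increase elsewhere; the planned difference-testing ANOVA has no criterion for 'equal', and the deciding measure varies between sections

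*Protocol article*

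**What the plan says.** All references are to the protocol article.

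**What is to be shown.** Primary hypotheses, item (iii), predicts that MATCH-ADTC will "Yield equal or better efficiency of service delivery". The Abstract (Background) gives the matching aim as to "increase the efficiency of service delivery", and the main Background speaks of demonstrating "increased efficiency of services". The Discussion also anticipates improved efficiency if results are positive.

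**How it is tested.** Under Statistical methods, Efficiency of service delivery, the two arms "will be compared using ANOVA to test for significant differences using the following data which will be collected from the clinical service". The only further provision is to transform data that do not meet the model's assumptions. No margin, equivalence bound or confidence-interval criterion is given.

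**Which measure decides.**
- Outcomes and measures, Primary outcomes, names one: "total time spent by clinicians delivering therapy (using therapy logs". The Abstract (Methods) agrees.
- The hypothesis names two: "this will be measured by clinician time (in minutes) to deliver therapy, and duration (in weeks) of contact with the service".
- The analysis section, under the heading Primary outcomes, lists four: clinician minutes, weeks of contact, number of sessions and number of missed sessions.

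**Sizing.** The revised sample size rests on the parent-rated Brief Problem Monitor alone: "This summary produced a standard deviation for the change in the parent-rated Brief Problem Monitor of 4.4". Nothing is sized for efficiency.

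**The concern.** A hypothesis of equal or better is met when the new treatment is no worse. A test of difference has no result that establishes this. Failing to reject is compatible with equality, but also with a worthwhile excess in clinician time that the trial was too imprecise to see. The 'equal' half of a primary hypothesis is therefore left without a valid route to a conclusion. Because the Abstract and Background use superiority wording, the same null result would fail one statement of the aim and remain unresolved under the other.

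The varying list of measures adds to this. Minutes and weeks could move in opposite directions, and the hypothesis and analysis sections do not say which would then settle the question. The Discussion connects positive results, including efficiency, to MATCH-ADTC becoming core training for clinicians, so the wording of this conclusion matters in practice.

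**Working it through.** **1. The plan's own figure.** The Sample size section uses SD 4.4, a difference of 2 and two-sided α = 0.05.

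Power = Φ(2 / (4.4 × √(2/n)) − 1.96), with n per arm.
- n = 80: 2 / (4.4 × √(2/80)) = 2.875, so power is Φ(0.915) = 82.0 % (stated 80 %).
- n = 100: 2 / (4.4 × √(2/100)) = 3.214, so power is Φ(1.254) = 89.5 % (stated 90 %).

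The stated sizing reproduces closely as a simple two-group comparison. It bears on the present point only because it fixes the total at 200.

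**2. Inputs for the efficiency comparison.**
- Participants: 200 (Sample size). Less 15 % attrition, 200 × 0.85 = 170.
- Clinicians: 60. Intraclass coefficient: 0.1. The Sample size section gives the attrition rate and this coefficient for the original sizing; carrying them over to the revised total and to clinician minutes is an assumption.
- Design effect: 1 + (170/60 − 1) × 0.1 = 1.183. Effective total: 170 / 1.183 = 143.7.
- Coefficient of variation (CV) of total minutes: not in the document. Assumed range 0.5, 0.7, 0.9.

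**3. Chance of a non-significant ANOVA if MATCH-ADTC truly takes 20 % more clinician time.** Analysis on log minutes, assuming log-normal data with the same CV in both arms, so that the log difference is the log ratio of means.

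SD(log) = √ln(1 + CV²); SE = SD × 2/√143.7 = SD × 0.1669; power = Φ(ln 1.2 / SE − 1.96), with ln 1.2 = 0.1823.

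| CV | SD(log) | SE | 0.1823/SE | Power | Non-significant |
|---|---|---|---|---|---|
| 0.5 | 0.472 | 0.0788 | 2.313 | 64 % | 36 % |
| 0.7 | 0.631 | 0.1054 | 1.730 | 41 % | 59 % |
| 0.9 | 0.770 | 0.1285 | 1.419 | 29 % | 71 % |

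The 95 % confidence interval for the ratio extends by a factor of exp(1.96 × SE) each way: 1.17, 1.23 and 1.29.

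**4. Check without the CV assumption.** Take 100 per arm, with no attrition or clustering, and let the true excess be d standard deviations. The probability of non-significance is approximately 1 − Φ(d/√(2/100) − 1.96). This is 71 % at d = 0.2, 44 % at d = 0.3 and 19 % at d = 0.4. The 95 % half-width is 1.96 × √(2/100) = 0.28 SD. Even under these favourable conditions, non-significance leaves room for a moderate excess.

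**5. What a non-inferiority comparison could support at this size.** With true equality and 80 % power, the ratio margin is exp((1.96 + 0.8416) × SE):
- CV 0.5: exp(0.221) = 1.25
- CV 0.7: exp(0.295) = 1.34
- CV 0.9: exp(0.360) = 1.43

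A margin of 1.20 would have power Φ(0.1823/SE − 1.96), that is 64 %, 41 % and 29 %.

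**The case against.** A reader might infer that the trialists intend to report a non-significant ANOVA as equal efficiency. The document does not say so, and the point should not be put that way. Nor is it right that the stated test cannot answer the hypothesis at all: a significant result for MATCH-ADTC supports 'better', and one against it contradicts 'equal or better'. Only the non-significant case is unresolved.

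The protocol never uses the term non-inferiority, and a difference test suits the superiority wording in the Abstract and Background. The fault is therefore an inconsistency about what is to be shown, and rewording the hypothesis is a legitimate and cheaper repair than adding a margin.

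It is also tempting to say that any of four measures could be chosen to support the claim. The formal outcome definition and the Abstract both name total clinician time alone, so what remains is a contradiction to reconcile. One could add that four tests at 5 % carry up to a 19 % chance of some false difference (1 − 0.95⁴ = 0.185). That assumes independence, which is unlikely for minutes, weeks and sessions, and it measures false differences rather than false equality. It is not relied on here.

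Finally, the Sample size section treats the trajectory of clinical severity as the primary question, and efficiency is a process outcome. This lowers the severity. What survives is that a declared primary hypothesis and its declared test do not fit. Both are stated in the article, so the mismatch is not detail left to a fuller plan.

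**Conclusion.** The point holds in limited form and should be fixed. The sections disagree on whether efficiency is to be equal or better, or increased, and on whether one, two or four measures decide. The stated ANOVA gives no valid support for 'equal' when it is non-significant. With 170 analysed, a design effect of 1.18 and CVs of 0.5 to 0.9, a true 20 % excess in clinician time would go undetected in about 36 % to 71 % of trials. The width of that range reflects the CV, which is assumed; the logic of the mismatch does not depend on it. The conclusion on clinical severity is unaffected.

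**What to change.** Keep total clinician minutes, as already defined under Outcomes and measures, as the sole deciding efficiency outcome. In the hypothesis and in the Efficiency of service delivery section, label weeks of contact, number of sessions and missed sessions as secondary. Then take one of two routes.

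(a) Reword hypothesis (iii) as superiority, in line with the Abstract and Background, and state that a non-significant result will not be reported as equal efficiency. This costs wording only, and gives up the equality claim.

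(b) Keep 'equal or better'. Before unblinding, set and justify a margin for the ratio of mean minutes, MATCH-ADTC to usual care. Make the claim only if the upper limit of the two-sided 95 % confidence interval lies below the margin, and then test superiority in sequence, which needs no further alpha. Otherwise report no conclusion. The cost is more than wording: with the sample fixed at 200, 80 % power under true equality needs a margin of about 1.25, 1.34 or 1.43 (assumed CV 0.5, 0.7, 0.9), so a tighter margin may often end in no conclusion.

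Neither route needs new data, and the article reports that recruitment is still open.

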## Methods

### Design

This study is a multi-site effectiveness randomized controlled trial comparing MATCH-ADTC with usual care [41]. Prior to randomization, written informed consent is obtained from each participant. Randomization is implemented on two levels: first, randomization of participating clinicians, then randomization of youth participants. For the randomization of clinicians, all clinicians from participating services were invited to participate and provide written informed consent. Consenting clinicians were block randomized (by service or team) in a 1:1 ratio to MATCH-ADTC or usual care. The block size varied across sites, depending on the number of individual clinicians recruited from each site. Clinicians were stratified on the basis of previous training in evidence-based therapies (i.e., those with versus those without training in cognitive behavioral therapy or behavioral parent training). Clinicians randomized to MATCH-ADTC received training in MATCH-ADTC at the beginning of the study prior to the recruitment of youth participants. Those randomized to usual care will receive training at the end of the study (once all follow-up data have been collected). Randomization of youth participants occurs after a clinician-administered eligibility check and once written consent has been obtained. Youth participants are then randomized in a 1:1 ratio to receive MATCH-ADTC or usual care, with participants stratified by sex and ethnicity (Māori, Pacific, or ‘other’). Web-based randomization procedures are used to determine treatment allocation. Data from all participants will be included in data analysis, irrespective of whether or not all assessments have been completed.

